##### iKT Focus Groups

Following cohort 1, we will invite participants to take part in iKT Focus Groups to generate user-informed feedback on the web-based AMT intervention and identify potential sex and gender differences in the user experience. Focus groups will be led by our sex and gender expert (RR) and use a semistructured, purposive, snowball sampling design. Half-day focus groups will be held in person, with dedicated focus groups for female and male participants to provide sex-stratified samples. We will limit focus groups to 5 participants, as previous research shows groups of 4-6 ameliorate the effects of “over sharing” or domineering participants, as well as participants who may feel intimidated and become silent within larger groups [89,90]. Groups will also include officers of the same rank, a sampling stratification strategy designed to help ensure interaction with others that are not perceived as threatening and with whom an individual’s experience may also resonate [90,91]. Focus group discussions will last between 60 and 120 minutes and will be voice-recorded to preserve their accuracy during transcription.

### Outcomes

In accordance with our hypotheses, PTSI (H1) will be measured by the PHQ-8, GAD-7, DASS-42, PCL-5, AUDIT, PSS, CBI, and self-reported stress visual analog scale. Self-reported resilience and well-being (H2) will be measured by the Brief COPE, RSA-33, BRS, WBSI, PTQ, UB-PSWQ, and UB-RRS. Functional wellness capacity and occupational stress will be measured by the SDS, GHPS, COVID-19 HRSI, WHODAS 2.0, PSQ, and LEAPS. Sex will be measured by self-reported sex at birth (male, female, or other); gender is measured by self-identification as male, female, nonbinary, or other (with the option to self-report) or “prefer not to disclose.” Sex and gender-related experiences will be measured by the WGDS and GEQ (H3 and H7). Changes in resting HRV (H4) will be measured by time and frequency domain parameters based on data collected from the wearable HR monitors (eg, high- and low-frequency HRV, low- or high- frequency ratio, and the Root Mean Square of Successive Differences, [RMSSD]) as recommended in the standards of practice for HRV analysis [17]. RSA (H5) will be measured by obtaining respiratory frequency. Greater power at the respiratory frequency indicates a higher level of RSA and will be analyzed using the gold standard HRV analysis program, Kubios [92]. Recovery from acute stress (H6) will be measured following completion of the web-based PASAT and emotional Stroop Tasks. Acute stress recovery will be assessed via a time-domain measure of HRV (RMSSD) [17].

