### Biological Resilience Training: Heart Rate Variability Biofeedback

Research reveals a connection between respiration, arousal, and emotional control, such that how a person breathes sends signals to regions in the brainstem and forebrain that modulate arousal [28]. For example, periods of slow breathing are associated with SNS suppression and PNS stimulation, which may underlie the anxiety- and stress-reducing effects of RSA [28]. For nearly 3 decades, Lehrer and Gevirtz [21] have pioneered and refined a cardiorespiratory intervention called heart rate variability biofeedback (HRVBF). During HRVBF, a person is shown visual feedback of their beat-by-beat HR data while engaging in slow breathing with the goal of maximizing RSA. For clinically effective treatment, it is not sufficient to simply instruct a person to breathe slowly. Rather, HRVBF technology is required to identify the precise breathing rate for maximizing individual RSA and to condition this rate through training [29,30].

In collaboration with expert police practitioners as well as medical and academic experts in psychophysiological risk and resilience, the lead author developed the International Performance Resilience and Efficiency Program (iPREP), an in-person resilience program that improves occupational health and performance by addressing the unique acute and chronic stressors faced by police [31-33]. This program has been refined across 6 grant-funded multimethod studies with over 300 police participants measuring objective psychophysiological and behavioral data [31-40]. The components of the currently proposed intervention are based upon the same core scientific principles and validated intervention methods as iPREP, including mental health awareness and support [2] and psychophysiological techniques (ie, HRVBF) to promote resilience by conditioning adaptive HRV, RSA, and HR functioning [30,41,42]. Research has shown that the autonomic modulation techniques instructed during iPREP result in significant, long-term reductions in occupational errors and improvements in officers’ ability to recover quickly from acutely stressful events when completed during scenario-based, in-person training [31-33].

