#### Objective Biological Indicators of PTSI Symptoms and Resilience

The following 4 hypotheses were proposed:

H4: Resting HRV will significantly increase following the completion of the AMT intervention.H5: RSA will significantly increase following the completion of the AMT intervention.H6: Recovery from acute stress will significantly improve following the completion of the AMT intervention.H7: Based on inconsistencies in the extant literature, we will conduct exploratory analyses of any potential sex and gender differences in HRV, RSA, and acute stress recovery at baseline and postintervention assessments.

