##### Session 2: Baseline Physiological Assessment and Introduction to AMT (40-60 Minutes)

All participants will be taught via web-based video modules how to apply the wearable HR monitor and configure the HRVBF app. The wearable HR monitor will automatically record date and time-stamped physiological data upon contact with the skin via the chest band and will communicate with the HRVBF app via Bluetooth. All HRV data will be stored locally on the HRVBF app and study device, which will be mailed back to the research team at the end of the study period. In the first part of this session, both experimental and control participants will provide baseline resting HRV and RSA data that will be recorded while participants engage in a 7-minute neutral activity (eg, listening to prerecorded sounds) that does not stimulate arousal or relaxation ([name], unpublished data, 2019). To assess recovery from an acute stressor, participants will perform web-based versions of the Paced Auditory Serial Addition Test (PASAT) [87] and the emotional Stroop task [88], both of which have been shown to induce significant sympathetic arousal but do not simulate traumatic material [28].

Following these baseline physiological assessments, participants in the experimental group will continue with the rest of their session (15-20 min) and begin the AMT intervention. Participants in the control group will not have any programming until session 8 (postintervention assessment).

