##### AMT Intervention Sessions 3-7 (45-60 Minutes Each)

These sessions will be completed by participants in the experimental group only. The content of each AMT session will be modified from the Lehrer et al [30] HRVBF protocol and informed by practitioner, knowledge user, and stakeholder-informed design workshops to adhere to iKT principles and fit a web-based format [42]. Participants will use the HRVBF app linked via Bluetooth to their HR monitor to engage in paced breathing exercises, view their RSA progress and live HRVBF data, engage with psychoeducational content on the LMS, and complete their homework assignments (ie, paced breathing practice at least twice a day as per protocol) [30]. Participants will also view short video lectures, text, and educational content, and engage in practical exercises during each session. Participants will receive weekly emails with practice reminders and links to useful resources, including links to YouTube videos of their preferred breathing pace. Participants will learn about meta-cognitive and coping skills as they can help mitigate stress in operational, organizational, and personal contexts to foster holistic resilience and well-being.

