##### Session 8: Postintervention Assessment (2 Hours)

All participants will receive an email reminder 1 week before the final session, which will be completed by both experimental and control participants. It will begin by obtaining objective physiological measures at rest, including HRV (7-minute neutral task), RSA (paced breathing), and recovery from acute stress (PASAT and Stroop tasks). Next, participants will complete the same self-reported questionnaires as in session 1 to assess changes in self-reported PTSI, resilience and well-being, occupational and operational stress exposure, and sex and gender-relevant data (see hypotheses). Participants in the control group will be asked if they would like to complete the AMT intervention. If so, they will be provided access to sessions 3 to 7 and will be asked to complete a second postintervention assessment (session 8) after completing the AMT intervention. Incentive payments will be processed as participants drop out or complete study assessments.

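### H4 predicts an increase in resting HRV with no lead index, over measures for which an increase does not mean the same thing, and breathing pace at rest is not addressed

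*Protocol article*

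**What the plan says.** All references are to the protocol article.

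- **Hypothesis.** Under Hypotheses, H4 reads "Resting HRV will significantly increase following the completion of the AMT intervention". No index is named.
- **Measures.** Outcomes assigns time and frequency domain parameters to H4, given as examples: "high- and low-frequency HRV, low- or high- frequency ratio, and the Root Mean Square of Successive Differences, [RMSSD]) as recommended in the standards". For H6 the same section settles on a single index: "Acute stress recovery will be assessed via a time-domain measure of HRV (RMSSD".
- **Analysis.** Data Security and Analyses gives resting HRV parameters, RSA and stress recovery separate repeated measures ANCOVAs. The covariates are sex, gender, age, years of service and service region. No expected direction per HRV index and no rule for mixed results is stated. Bonferroni correction is promised where applicable, without a defined family.
- **Recording.** Session 2 takes resting HRV during a "7-minute neutral activity (eg, listening to prerecorded sounds) that does not stimulate arousal or relaxation". Session 8 lists "HRV (7-minute neutral task), RSA (paced breathing), and recovery from acute stress (PASAT and Stroop tasks".
- **Training.** HRVBF means "engaging in slow breathing with the goal of maximizing RSA", at an individual rate that is then conditioned. Sessions 3-7 add "paced breathing practice at least twice a day as per protocol". Controls have no programming between the first part of session 2 and session 8.

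**The concern.** Two features combine.

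First, H4 commits to one direction, but the measures attached to it do not share one. HF power is part of the low/high ratio, so a gain in HF pushes the ratio down unless LF grows at least in proportion. With no lead index, the same data could be reported as supporting H4 or as going against it.

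Second, the intervention trains a slow breathing pace in one arm only. The article itself treats breathing as physiologically active ("periods of slow breathing are associated with SNS suppression and PNS stimulation") and defines RSA as HRV power at the respiratory frequency. An officer who slips into the trained pace during the session 8 neutral task could therefore show different HRV values because of how he or she breathed in those 7 minutes. Untrained controls have no matching shift, so randomisation and the control arm do not cancel it.

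At stake is what a significant H4 result would mean: a change in resting autonomic function, or a change in breathing during the recording.

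**Working it through.** **1. The plan's own figure.** The article gives no figure for this point. The nearest is the minimum sample of 128 in Recruitment (f = 0.25, α = .05, power 0.80, two groups). With λ = f²N = 0.0625 × 128 = 8 and 1 and 126 degrees of freedom, the noncentral F gives power 0.801, so 128 reproduces as one two-group comparison of one index at 0.05. If any of the four example indices could confirm H4:
- unadjusted error is 1 − 0.95⁴ = 0.185, taking the tests as independent;
- Bonferroni gives 0.05/4 = 0.0125, which needs 182 for 80% power. Power is 0.62 at 128 and 0.92 at the planned 250.

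A single named index leaves 128 unchanged.

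**2. Direction of the ratio.** New ratio / old ratio = (LF multiplier)/(HF multiplier).

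| LF × | HF × | LF/HF × |
|---|---|---|
| 1.0 | 1.2 | 0.83 |
| 1.2 | 1.2 | 1.00 |
| 1.5 | 1.2 | 1.25 |

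All three can rise, but only if LF rises proportionally more than HF. A gain in HF alone lowers the ratio. If the printed ratio is read the other way round (HF/LF), a gain in LF alone lowers it (1/1.2 = 0.83), so the conflict remains.

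**3. Breathing pace, illustration only.** The article gives no band limits, no trained rate and no resting rate. Assumed: band edge 0.15 Hz; mean RR interval T = 0.9 s; non-respiratory power 500 ms² at 0.09 Hz (LF) and 100 ms² at 0.27 Hz (HF); respiratory power 600 ms², held constant, at breathing frequency f. Respiratory power counts as HF if f ≥ 0.15 Hz and as LF otherwise. RMSSD² ≈ Σ P(f) × [2 sin(π f T)]².

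The non-respiratory part of RMSSD² is 500 × 0.2535 + 100 × 1.912 = 317.9. The respiratory part is 600 × 1.687 = 1012.3 at 0.25 Hz, 600 × 0.824 = 494.7 at 0.167 Hz, and 600 × 0.3113 = 186.8 at 0.10 Hz.

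| Breaths/min | LF (ms²) | HF (ms²) | LF/HF | RMSSD (ms) |
|---|---|---|---|---|
| 15 | 500 | 700 | 0.71 | 36.5 |
| 10 | 500 | 700 | 0.71 | 28.5 |
| 6 | 1100 | 100 | 11.0 | 22.5 |

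**4. When the sign of RMSSD turns.** Training aims to enlarge RSA, so constant power is only one case. At 6 breaths/min, RMSSD returns to its value at 15 when respiratory power grows by [sin(π × 0.25 × 0.9)/sin(π × 0.10 × 0.9)]² = (0.6494/0.2790)² ≈ 5.4, an amplitude factor of √5.4 ≈ 2.3. With 4-fold power, RMSSD = √(317.9 + 4 × 186.8) = 32.6, still below 36.5. With 8-fold power it is √(317.9 + 8 × 186.8) = 42.6, above it.

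**5. Sections side by side.** Session 2 records RSA together with resting HRV in the neutral activity; session 8 attaches RSA to paced breathing. So although Outcomes obtains respiratory frequency for RSA, the article does not establish that it is available for the session 8 neutral segment. The equipment described is a heart rate monitor with a chest band, with no separate respiration sensor.

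**The case against.** The strongest defence has four parts.

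- **The list is illustrative.** A reader might infer that all four indices must rise together for H4 to hold. The text does not say so: they are examples, tested separately, and nothing states that a higher ratio counts as success. That stands against the stronger reading. It does not supply a lead index, and H6 shows that the article names one when it means to.
- **Rest is kept apart from paced breathing.** A reader might infer that slow-breathing training necessarily drives the indices apart, or that H4 will be decided by breathing pace alone. The documents do not support either. The resting task is neutral and unpaced, and whether officers breathe slowly in it is unknown. At 10 breaths/min the assumed bands do not move, and a large enough RSA gain reverses the sign of RMSSD. This stands, so the mechanism is a plausible confounder and not an established one.
- **Adjustment is awkward.** Breathing rate at session 8 may itself be changed by the intervention, so adjusting for it could remove part of a real effect. This stands and limits adjustment to a sensitivity role.
- **An article condenses.** Band definitions and participant scripts may sit in a fuller document, and an instruction already there would answer the breathing part. But the direction of H4 and its measures are printed here, and an analysis plan cannot restore afterwards how participants breathed during recording.

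**Conclusion.** The point holds in limited form and is worth acting on. That H4 lacks one usable direction follows from the article's own text and from algebra: with LF unchanged, HF × 1.2 takes LF/HF to 0.83, a success on one listed measure and a failure on another.

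The breathing part is conditional. It needs trained officers to carry a slower pace into the session 8 neutral task. If they do, the shift arises in the trained arm only and the waitlist comparison does not remove it. Its size and sign cannot be fixed from the documents: in the illustration they run from no band change (10 breaths/min, RMSSD 28.5) to HF 700 to 100, LF 500 to 1100 and RMSSD 36.5 to 22.5 (6 breaths/min, constant respiratory power), with RMSSD rising once respiratory power grows more than about 5.4-fold. These values rest on the assumed band edge, RR interval and powers.

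**What to change.** - In Hypotheses and Outcomes, name one H4 index with its direction, for example an increase in RMSSD, which already serves H6. Do not let an increase in LF or in LF/HF confirm H4; report both descriptively.
- In the neutral task at sessions 2 and 8, ask both arms to breathe normally and not to use paced breathing.
- Derive breathing frequency in that segment where the recording allows, report it by arm, and use it only in a sensitivity analysis, because the session 8 value is measured after randomisation and may be changed by the intervention.

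The cost is a line in the web task script, a wording change in the outcomes, and some extra processing where breathing frequency can be derived. Fewer HRV parameters can then be claimed as H4 successes. Cohorts tested before the instruction is added are not covered by it; the Results section reports 7 pilot registrants by April 2023.

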### Data Security and Analyses

Any personally identifiable information provided in the eligibility questionnaire will be downloaded and immediately deleted from web-based platforms, stored offline in encrypted files on password-protected computers at the University of Toronto accessible only by members of the primary research team approved by the lead principal investigator (JPA), and will not be shared with collaborators or participating police organizations. Data collected on the LMS and secure survey platforms (ie, pre- and postintervention assessments and responses to intervention exercises) will be matched to a deidentified user ID. Physiological data gathered by the wearable HR monitor and HRVBF app will be stored locally and will not be transferred to publicly accessible third-party cloud-based servers. Rather, participants will mail the equipment back to the research team, which will match the deidentified data offline. The key code linking participants’ personal information and deidentified user IDs will only be stored on secure servers at the University of Toronto and will be destroyed once the participant completes or withdraws from the study, has received their compensation, and all deidentified data files have been matched.

Physiological data will be transferred to a 2-time Canada Research Chair in Health Informatics and Big Data expert coinvestigator (CM) via a secure virtual private network (VPN) tunnel and housed on a private cloud-based Big Data analytics platform located within the *Compute Ontario Advanced Research Computing* equipment at the Centre for Advanced Computing (Queen’s University). CM will design the data management, cleaning, and analysis protocols necessary to construct the big data pipeline to process the large amount of continuous data, including matching the time stamps on the physiological data to significant event markers in the AMT intervention (eg, questionnaires, PASAT, and emotional Stroop tasks) and on the HRVBF app (eg, paced breathing exercise). Preprocessed data will then be sent back to the primary research team (JPA, PMD, and SCS) via a secure VPN tunnel and housed on the secure internal University of Toronto server (RES-NAS) for the statistical analyses described below using bespoke syntax and code on various software platforms (eg, Kubios, MatLab, and SPSS). Data from iKT focus groups will be stored in RR’s secure data web-based Al Fresco space and hard copies in her triple-locking filing cabinet in her office at the Memorial University of Newfoundland.

To test the effectiveness of the AMT intervention on reducing PTSI symptoms and improving resilience, we will conduct prepost analyses of the self-reported PTSI (H1) and resilience measures (H2) using separate repeated measures analyses of covariance (ANCOVAs) accounting for demographic covariates for normally distributed data, and ranked repeated measures ANCOVAs for nonnormally distributed data [93]. Variables including sex, gender (H3), age, years of service, and geographic service region (eg, urban or rural; East, Central, or West) will be included as covariates.

To test the effectiveness of the AMT intervention on improving biological indicators of resilience, prepost analyses of resting HRV parameters (H4), RSA (H5), and recovery from acute stress (H6) will be separately assessed using repeated measures ANCOVAs with sex, gender (H7), age, years of service, and geographic service region as covariates. To determine which factors significantly predict greater changes in biological outcome measures, hierarchical linear regression analyses will be undertaken with self-reported measures and demographic variables entered as predictors in the models. We will also compare weekly changes in HRV and RSA as measured during AMT module exercises with repeated measures ANCOVAs. A main effects analysis of the “time” variable will explore the potential incremental benefit of AMT training and identify at what point during the 6-week intervention significant biological changes occur. Computational approaches to analyzing and visualizing biological indices of resilience will be led by CM, including integration of cardiac (eg, HRV) and respiratory (eg, RSA) rhythms to elucidate patterns of desynchronization before, during, and following AMT.

To explore sex and gender-based contributions to self-report (H3) and objective indices (H7) of PTSI and resilience, the above analyses will include sex and gender as covariates or predictor variables with sex-stratified samples. These findings will clarify any sex-related differences in baseline and postintervention rates of PTSI and resilience among law enforcement officers and whether there are any sex-related differences in the magnitude of treatment effects (H3). Moderated regression analyses will test whether the AMT intervention affects the relationship between sex and PTSI symptoms and resilience. Multiple comparisons will be adjusted with Bonferroni corrections, where applicable.

Qualitative analyses of the transcribed data obtained from the iKT focus groups will be led by the sex and gender coinvestigator (RR) with the assistance of graduate students and postdoctoral fellows, with the aim of identifying sex- and gender-based considerations for developing effective occupational health interventions tailored to police officers and other PSP groups. Qualitative data analysis will use an inductive, comparative approach without initially arriving at any definitive, substantive, or theoretical conclusions about what the data reflect interpretatively with a lens on sociology and criminology [94]. Themes will emerge through the dynamic interaction of participants. Coding will be performed using NVivo qualitative analysis software (Lumivero), allowing for comparison across sessions [89] and the emergence of prominent themes through the tracking of coding “nodes” both across and within groups. Regular research team meetings will ensure that thematic development emerges in a consistent and reliable manner and help to ensure the hermeneutically attuned validity of the data [90].

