### Hypotheses

#### Self-reported PTSI Symptoms and Resilience

The following 3 hypotheses were proposed:

H1: Symptoms of PTSI will be significantly reduced following the completion of the AMT intervention.H2: Functional wellness capacity and resilience will be significantly improved following the completion of the AMT intervention.H3: Sex and gender differences in PTSI will be observed at baseline and postintervention assessments.

Specifically, we expect that self-identified females will report more symptoms of PTSI and lower resilience at baseline, a greater reduction of PTSI symptoms, and a greater increase in resilience at follow-up than self-identified males. Gender role stress, discrimination, and harassment will be explored as moderators of PTSI symptoms at baseline and in response to the AMT intervention.

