### Design

Capitalizing on the numerous long-standing professional relationships between study coinvestigators and police populations of interest, phase 1—development of the AMT intervention—will use an integrated knowledge translation (iKT) approach to generate user-informed content [42]. To test the effectiveness of the AMT intervention (phase 2), a cluster randomized control trial with parallel assignment will be used on several cohort samples of active-duty Canadian police officers. This study has been registered with ClinicalTrials.gov (NCT05521360).

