### Recruitment

We aim to test the AMT intervention on a sample of approximately 250 frontline police officers in rolling cohorts of 10-15 participants (half AMT, half waitlist control) from geographically representative police services across Canada. A power analysis was conducted using G*Power software [43] and found that a minimum total sample size of 128 participants was required (effect size f=0.25, α=.05, power=0.80, number of groups=2, number of repeated measures=2). However, we plan to oversample officers by sex and mitigate possible attrition based on the principal investigator’s previous experience with conducting longitudinal research on police officers [31-33]. A small laboratory-based prepilot sample (n=10) will test equipment reliability, accuracy, and integration of HR monitors with HRVBF and learning management system (LMS) platforms. An initial pilot cohort 1 (n=30) will then test the AMT intervention in the population of interest (ie, law enforcement officers) using a combined laboratory-remote paradigm to validate the implementation of study procedures. These participants will also be invited to participate in a poststudy focus group as per the study protocol (see iKT Focus Groups in Procedures) to optimize the intervention (ie, content and delivery) and overall study procedures to provide stakeholder- and user-informed feedback. When all user feedback has been incorporated, all subsequent participants will be tested fully remotely and in accordance with the randomized control trial procedures and group allocation.

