### Inclusion and Exclusion Criteria

Inclusion criteria included adults (aged 18 years or older) currently employed as active duty (ie, not retired or on an extended medical or disability leave) frontline law enforcement officers fluent in English. Exclusion criteria include non-Canadian law enforcement officers, police administrators, civilian employees (ie, nonsworn members), and officers that do not have regular access to a computer with internet access to complete the web-based AMT intervention. Scores on self-reported mental health screening tools completed during the preintervention sessions will be used to match the assignment of participants to experimental or control groups but will not be used to exclude participants based on established cutoff scores for high or severe PTSI symptoms.

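### The tests of H1, H2 and H4–H6 do not name the AMT-versus-waitlist contrast; read as group-by-time they are valid but forgo baseline adjustment

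*Protocol article*

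**What the plan says.** For self-report, Data Security and Analyses says: "we will conduct prepost analyses of the self-reported PTSI (H1) and resilience measures (H2) using separate repeated measures analyses of covariance", with a ranked version for non-normal data. The covariates are introduced as "Variables including sex, gender (H3), age, years of service, and geographic service region". For physiology, "prepost analyses of resting HRV parameters (H4), RSA (H5), and recovery from acute stress (H6) will be separately assessed using repeated measures ANCOVAs", with the same covariates. Neither sentence mentions arm, and neither lists the outcome's own baseline value as a covariate. The only model effect singled out by name in that section is a main effect of time, and it concerns the weekly data from the AMT modules.

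The hypotheses have the same form. H1 reads: "Symptoms of PTSI will be significantly reduced following the completion of the AMT intervention". H2 and H4–H6 likewise predict improvement after AMT without reference to the waitlist.

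The design, however, is comparative. Under Design, "a cluster randomized control trial with parallel assignment will be used", and under Recruitment the sample is taken in "rolling cohorts of 10-15 participants (half AMT, half waitlist control"). The power calculation there uses two groups and two repeated measures, with f=0.25, α=.05 and power 0.80, and arrives at 128. Under Inclusion and Exclusion Criteria, baseline mental health scores "will be used to match the assignment of participants to experimental or control groups".

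**The concern.** A randomised trial with a waitlist arm answers one question: did officers given AMT end up better than officers who waited? The analysis text gives the model family, the covariates, a rank alternative and a multiplicity adjustment, but it omits the term that answers this question. Together with hypotheses about change after AMT, it leaves open whether a hypothesis is confirmed when AMT officers changed or when they changed more than controls.

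The choice matters. Repeated testing, regression to the mean and shared operational or seasonal changes move both arms. A pre-post test credits that movement to AMT, and the waitlist arm exists to remove it. If the group-by-time term is meant, the problem is smaller: the comparison is sound but uses the baseline score inefficiently.

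**Working it through.** **Inputs from the article:** f=0.25, α=.05, power 0.80, two groups, two measures, minimum 128, planned total about 250, split half and half (125 per arm). **Assumed, because the article gives neither:** the pre-post correlation r (range 0.3 to 0.8) and the size of any common drift. Scores are in SD units with equal variance at both waves. Participants are treated as independent and all as completing.

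**1. The plan's own figure.** For a two-group test with 1 numerator df, λ = f²N = 0.0625 × 128 = 8. With 1 and 126 df the power is 0.8015, so 128 is reproduced. For two groups f=0.25 corresponds to d=0.5. The sample size therefore presupposes a between-group contrast.

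**2. Reading A: pre-post change or a time effect.** Within n participants, the mean change has variance 2(1−r)/n. With no AMT effect and a common drift δ, z = δ/√[2(1−r)/n]. For δ=0.2, r=0.6, n=125: z = 0.2/√(0.8/125) = 0.2/0.08 = 2.5, and the probability of significance is Φ(2.5−1.96) = Φ(0.54) ≈ 0.70. For δ=0.1 and 0.3, z is 1.25 and 3.75, giving 0.24 and 0.96. At r=0.5 and δ=0.2 the AMT arm alone gives 0.60, and a time effect pooled over both arms gives 0.88.

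**3. Reading B: group-by-time.** With two waves this term is the difference between arms in mean change. Per participant, the relevant variances are:

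- change score: 2(1−r)
- final score adjusted for baseline: 1−r²
- ratio: 2(1−r)/(1−r²) = 2/(1+r)

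| r | change score | baseline-adjusted | ratio | N for d=0.5, 80% power (change / adjusted) | detectable d at N=250 (change / adjusted) |
|---|---|---|---|---|---|
| 0.3 | 1.40 | 0.91 | 1.54 | 178 / 118 | 0.42 / 0.34 |
| 0.5 | 1.00 | 0.75 | 1.33 | 128 / 98 | 0.35 / 0.31 |
| 0.8 | 0.40 | 0.36 | 1.11 | 54 / 48 | 0.22 / 0.21 |

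Detectable d is 2.80 × √(4v/250), where v is the variance in the row. Put the other way, adjustment removes (1−r)/2 of the change-score variance: 35%, 25% and 10% in these rows.

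**4. Effect of matching.** Since 2(1−r) = (1−r²) + (1−r)², the extra term (1−r)² is the part due to chance baseline differences between arms. To the extent that matching on session 1 scores removes those differences, a change-score analysis still carries the term in its standard error, and its intervals are wider than they need be. Adjusting for baseline lets the analysis reflect the allocation. This applies to the self-report outcomes; the physiological baseline is taken in session 2, after allocation.

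**The case against.** The strongest reply is that the contrast is unnamed, not excluded. The design is parallel and randomised, controls complete both assessments, the power inputs specify two groups, the abstract describes the control condition itself in pre-post terms, and later analyses refer to the magnitude of treatment effects and include AMT in moderated regressions. A reader might infer from the analysis text that the trial plans no comparison with the waitlist. The document does not support that: taken as a whole it points to a two-group model, and a condensed article may leave model terms to a fuller plan. This part of the reply stands, and it makes Reading A the less likely one.

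It is also fair that a group-by-time test is a valid estimate of the AMT effect under randomisation, that baseline is already one of the two measures, that the covariate list is introduced as non-exhaustive, and that about 250 planned against 128 leaves room. The precision loss alone would be a modest matter.

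The reply does not remove the mismatch. The hypotheses and the test sentences that the article does give both describe within-person change, and nothing in them commits the trial to the comparison on which its sample size rests. Even the favourable reading leaves an avoidable loss.

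**Conclusion.** The concern holds as an unnamed contrast that does not match the two-arm design and the two-group sample size. Its size depends on the reading. As a time effect, the test does not isolate AMT: an assumed 0.2 SD drift alone is declared significant about 70% of the time at n=125 and r=0.6. As group-by-time, the test is valid but has 1.54 to 1.11 times the variance of a baseline-adjusted analysis for assumed r of 0.3 to 0.8.

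A reader might want to hold both faults against the plan at once. That does not follow, because no single model has both. A reader might also infer that a time effect would be tested at age zero and service zero because covariates are left uncentred. The article says nothing on covariate coding, and centring does not affect the group-by-time test, so that point is not made here.

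**What to change.** Reword H1, H2 and H4–H6 as AMT versus waitlist at session 8. For controls this means the first session 8 assessment, before any take-up of AMT. State that the test of each is the arm difference adjusted for the participant's own baseline value (session 1 for self-report, session 2 for physiology), and keep the planned demographic covariates. Name the same contrast for the ranked version.

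Two forms are suitable:

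- ANCOVA on the session 8 score, with arm and baseline value in the model. It uses only participants with a session 8 value, as a standard two-wave repeated-measures ANCOVA does.
- A longitudinal mixed model of both waves with baseline means constrained equal across arms. It also retains participants who have a baseline but no session 8 value.

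These are not equivalent under attrition, which the Recruitment section anticipates, so one should be declared primary. Neither recovers physiological data for participants who leave after allocation but before session 2. Adding the baseline score as a covariate to a repeated-measures model that already contains it as an outcome is not the right form.

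Label the AMT-only weekly time trends as descriptive. The cost is revised hypothesis and analysis wording before the data are analysed; no new data collection is needed.
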